##### EEG assessments

After behavioral assessment at pre- (1st session), mid- (7th session), end- (13rd session), and follow-up sessions (2 and 6 weeks after the end of the intervention), EEG data will be recorded while participants listen to a passive oddball paradigm. Emotional and neutral words uttered by human voices recorded at Stage 1 will be displayed to the participant. During the EEG recording, participants will sit on an armchair while watching a silent movie and will be instructed to pay no attention to the auditive stimuli. One stimulus block containing 1,200 words will be presented for an approximately 20-min paradigm. It will consist of 960 frequently presented neutral-uttered standard stimuli (80%), and occasional 48 anger (4%), 48 disgust (4%), 48 fear (4%), 48 happiness (4%), and 48 sadness (4%) deviant stimuli. Standard and deviant stimuli will be equally uttered with a male, woman, or child voice. The stimuli will be presented pseudo-randomly with deviant stimuli being preceded by at least two standard stimuli. The stimulus sequence will not vary between participants. The stimulus onset asynchrony will be of 1,300 ms. The stimuli will be presented at 60 dB via the Shure SRH1840 audio headset. Autistic participants will be accompanied by their parent if necessary.

Electroencephalographic recording and processing will follow the same methodology as the one described in section “EEG Recording and Processing.”

#### Social Stories^TM^ Elaboration

Figure 2 illustrates the process that will be used to generate the Social Stories^TM^ before their use in the intervention.

**FIGURE 2 F2:**
[figure not shown]
Process for Social Stories^TM^ elaboration before their use in intervention. TD, Typically developed.

##### Content

Social Stories^TM^ content will follow the ten criteria established by Gray (2015). Three general Social Stories^TM^ and six specific patterns will be initially written and will serve as basis for further child personalization. According to Carol Gray, each social story will contain three types of information: “The News,” “Ways to Think About The News,” and “Connections and Implications.” The News is an objective description of the social scenario that is trained. Ways to Think About The News is an indication of how managing The News adequately. Finally, Connections and Implications reference past, present, and future concrete examples of the social scenario that is trained in order to foster understanding and future correct behavior. Each Social Story^TM^ will be composed of an introduction, body part, and conclusion (Pane et al., 2015) in order to unsure a structured and logic design. Considering the age of the participants, Social Stories^TM^ will be made of at least 12 first and third-person perspective sentences that can be descriptive, perspective, coaching, affirmative, partial, or interrogative (Gray, 2015). To reach personalization to the child, relevant information about the child (e.g., interests, emotional usual behaviors) will be previously gathered by communicating with the parents. Then, three general and six specific Social Stories^TM^ will be written for each child. After writing them, they will be sent to the parents who will be asked if they wish to modify their content in order to foster the personalization to their child. Also, the child and parents will be free to add one or two sentences based on personal experience that would help to remember the information. Please see Supplementary Files 1, 2 for examples of a Social Story^TM^ and questions for the parents, respectively.

##### Recording and edition

Personalized and initial patterns of Social Stories^TM^, and all other robot speech will be recorded from volunteer actors: one adult male, one adult female, and one child, depending of the characteristics of the synthesized voices selected in Stage 2. They will be asked to read and get grips with the entire set of utterances and will be given as much time as he/she needs. Then he/she will be instructed to read each utterance with an adequate intonation. The emotional or neutral prosodies will be specified across the text. Participants will be asked to do their best possible to get into the emotional role. All specific utterances from a particular emotion will be uttered successively in order to facilitate this process. Participants will be asked to wait at least 5 s between two readings in order to focus before each recording. The recording material and environment will be the same than the one described in Stage 1.

Neutral and emotional synthesized speech uttered by the robot during the intervention will be obtained by editing acoustic features of the previous recordings in order to reach the same characteristics as neutral and emotional voices selected in Stage 2. The same methodology for synthesized voices creation as the one described in Stage 2 will be followed. The frequency response of the acoustic signal that comes from the robot’s speaker will be computed using Matlab. The frequency response will determine the deformation of the intensity of the sound by the speaker as a function of frequencies. Audio signals will be edited in order to compensate this bias generated by the speaker.

##### Validation

The previously created Social Stories^TM^ will be checked for adequacy regarding the understanding of emotions conveyed. TD children will take part to the validation task procedure. Participants will interact with NAO which will tell the Social Stories^TM^ with the adequate emotional prosody (please see Supplementary File 1 for an example of the prosody variations across a Social Story^TM^) uttered by the human voice from original recordings after the robot speakers frequency response compensated. For each story, the number of correct recognitions of emotions (correct/incorrect answers to the questions inserted in the story) will be counted. Before the beginning of the task, instruction will be explained. Particularly, it will be told to the participants that the stories are personalized for another child, so that they do not have to consider personalized sentences as directed to them. However, their task will be to answer the robot question about which emotion will be conveyed by the prosody. Correct responses will lead to social reinforcement. Each story and question will be told once to the participant. Each participant will listen to nine Social Stories^TM^ (patterns for three general and six specific stories) for an approximate 45-min session.

For number of correct/incorrect responses comparisons, a one-way ANOVA will be conducted for each Social Story^TM^ separately. Normality and homogeneity of variances will be assessed by Shapiro–Wilk and Bartlett tests, respectively. In case of non-parametric distribution of the data, Kruskal–Wallis test will be applied. *Post hoc* comparisons will be conducted to assess specific differences (Tukey after ANOVA, Wilcoxon tests with *p*-value adjustment by Holm method after Kruskal–Wallis). Level of significance will be set at *p* < 0.05. If a Social Story^TM^ does not reach significance, it will be modified and validated again.

#### Data Analysis

##### Statistical analysis on ASRS scores

Group comparisons will be conducted by one-way ANOVAs on T-scores for each assessment session and symptom domain (Social/Communication, DSM-IV-TR, Peer and Adult Socialization, and Social/Emotional Reciprocity) separately.

Time comparisons (between assessment sessions) will be tested by one-way ANOVAs on T-scores for each group and symptom domain (Social/Communication, DSM-IV-TR, Peer and Adult Socialization and Social/Emotional Reciprocity) separately.

Normality and homogeneity of variances will be assessed by Shapiro-Wilk and Bartlett tests, respectively. In case of non-parametric distribution of the data, Kruskal-Wallis test will be applied. Post-hoc comparisons will be conducted to assess specific differences (Tukey procedure in case of ANOVA, Wilcoxon tests with *p*-value adjustment by Holm method in case of Kruskal–Wallis test).

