#### Participants

Typically developed participants will be recruited from a public announcement posted on Tecnologico de Monterrey, Campus Monterrey. Autistic participants will be recruited by contacting parents of autistic children attending San Jose Hospital from Tecnologico de Monterrey.

Sample size estimation was calculated with G^∗^Power software version 3.1.9.7 (Faul et al., 2007) for Cohen’s d effect size index of 0.8, correlations among repeated measures of 0.5, statistical significance set at *p* < 0.05. For level comparisons, results indicated that 20 participants in each group would be enough to provide an estimated power of 0.90. For group comparisons, results indicated that 38 participants in each group would be enough to provide an estimated power of 0.91.

Forty high-functioning autistic volunteers aged 9 to 11-year-old will be involved in this stage of the research. All autistic participants will be diagnosed by a clinician according to DSM-V (Diagnostic and Statistical Manual of Mental Disorders, Fifth Edition) (American Psychiatric Association, 2013) or the International Classification of Diseases and Related Health Problems – Tenth Edition (World Health Organization, 1994) criteria. Autistic symptomatology will be assessed by the Autism Spectrum Rating Scales (ASRS) – parent report (Goldstein, 2012). A T-score greater than 60 (slightly elevated to very elevated scores for autistic behaviors) on Social/Communication, DSM-IV-TR (Text Revision), Peer and Adult Socialization and Social/Emotional Reciprocity domains will be considered as an inclusion criterion.

In addition, 40 TD volunteers aged 9 to 11-year-old will be included in this study. Similar to autistic children, ASRS will be used, and children with a score inferior to 60 in all scales will be included.

Any TD or autistic participant will be excluded if child:

•is under medication affecting the central or peripherical nervous system,•has hearing loss or deficits, and/or•has history of a developmental pathology and/or any disease affecting behavior and nervous system, apart from ASD for autistic participants.

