
#### Outcome Measures

##### ASRS questionnaire

The ASRS questionnaire is a standardized, reliable and validated set of questions targeted to parents or teachers of autistic people aged between 2 and 18 years to measure their autistic symptomatology (Simek and Wahlberg, 2011). It presents several advantages for its use in research (Goldstein, 2012). First, a wide range of autistic social and emotional behaviors are assessed, so that it makes the evaluation of generalization of learning to other social domains possible. Second, the scores provided are based on a normative TD sample, thus it considers the autism spectrum as a continuum with the general population making possible the comparison with a TD control group. The full-length version for 6–18 years old children and youths is composed of 71 items divided in three scales: ASRS scale, DSM-IV, and Treatment Scale. A 4-level scale is presented to the rater in order him to specify how often a particular behavior is used to be observed in the child or youth that is evaluated. Higher scores indicate higher symptoms severity according to the rater. In this study, a particular focus will be dedicated to Social/Communication, DSM-IV-TR, Peer and Adult Socialization and Social/Emotional Reciprocity domains. Parents of both groups will answer this questionnaire on pre-intervention (1st session) and follow-up sessions (2 and 6 weeks after the end of the intervention).

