##### Intervention

Autistic and TD participants involved in this study will have to meet the same criteria than those described in Stage 2. However, participants from Stage 2 will not be included in Stage 3 in order to avoid any bias elicited by a former exposition to the synthetic voices under study.

Sample size estimation was calculated with G^∗^Power software version 3.1.9.7 (Faul et al., 2007) for Cohen’s d effect size index of 0.8, correlations among repeated measures of 0.5, and statistical significance set at *p* < 0.05. For ERP analysis, results indicated that 13 participants in each group would be enough to provide an estimated power of 0.92 for group comparisons, and 11 participants in each group would be enough to provide an estimated power of 0.91 for assessment sessions comparisons. For behavioral analysis on reaction times, results indicated that 13 participants in each group would be enough to provide an estimated power of 0.91 and seven participants in each group would be enough to provide an estimated power of 0.93 for assessment sessions comparisons. For behavioral analysis on number of correct/incorrect answers, results indicated that 18 participants in each group would be enough to provide an estimated power of 0.92 for group comparisons, and 15 participants in each group would be enough to provide an estimated power of 0.90 for assessment sessions comparisons (Cohen’s d effect size index of 0.8, statistical significance set at *p* < 0.05). For behavioral analysis on ASRS scores, results indicated that 16 participants in each group would be enough to provide an estimated power of 0.92 and 18 participants in each group would be enough to provide an estimated power of 0.90 for assessment sessions comparisons.

A total of 72 participants will take part to this Stage and will be divided in four groups:

•Group 1: autistic children receiving robot, synthesized and human voices intervention (18 participants).•Group 2: autistic children receiving robot and human voice intervention (18 participants).•Group 3: autistic children without receiving intervention (18 participants).•Group 4: TD children without receiving intervention (18 participants).

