Group 1 will be the experimental group and groups 2–4 will be controls. Children from group 2 will receive the same intervention as children from group 1, with the exception of the use of human voices only. This group will help to evaluate the efficacy of the use of synthesized voices in the intervention. Autistic participants will be randomly assigned to any of groups 1, 2 or 3. All four groups will be included in pre-, mid-, end and follow-up assessments.

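### The Stage 3 ASRS group ANOVA appears to include the TD group, which is selected on the same ASRS domains, so its omnibus result says nothing about efficacy and its stated power does not cover the randomised contrasts

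*Protocol article*

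**What the plan says.** **Entry.** The Stage 2 Participants section admits autistic children on "A T-score greater than 60 (slightly elevated to very elevated scores for autistic behaviors) on Social/Communication" and three further domains: DSM-IV-TR, Peer and Adult Socialization, and Social/Emotional Reciprocity. For TD volunteers, "children with a score inferior to 60 in all scales will be included". Stage 3 adopts these rules: "Autistic and TD participants involved in this study will have to meet the same criteria than those described in Stage 2".

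**Outcome.** In the ASRS questionnaire section, "a particular focus will be dedicated to Social/Communication, DSM-IV-TR, Peer and Adult Socialization and Social/Emotional Reciprocity domains". These are the same four domains, from the same parent form, collected at the 1st session and 2 and 6 weeks after the intervention ends.

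**Analysis.** "Group comparisons will be conducted by one-way ANOVAs on T-scores for each assessment session and symptom domain". Then: "Post-hoc comparisons will be conducted to assess specific differences (Tukey procedure in case of ANOVA", with Holm-adjusted Wilcoxon tests if Kruskal–Wallis is used instead. Time comparisons are made separately within each group.

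**Groups.** The Intervention subsection lists four groups of 18, the last being "Group 4: TD children without receiving intervention (18 participants"). It adds: "Group 1 will be the experimental group and groups 2–4 will be controls". Only autistic children are randomised, to Groups 1, 2 or 3. All four groups attend the assessments.

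**Power.** For the ASRS group comparison, 16 per group is said to give 0.92. The paragraph opens with d = 0.8 and a 0.05 significance level; the ASRS sentence does not restate the effect size or give the number of groups.

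**The concern.** One instrument, on the same four domains, both sorts children into autistic and TD and is then compared between them. If Group 4 is in the ANOVA, the null hypothesis of equal means is already contradicted by the eligibility rules. There are 3 sessions × 4 domains = 12 such group tests, and significance across them would be expected with an intervention that does nothing.

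Two things follow for the randomised question. The Tukey family has six pairs instead of three, and three of the six involve TD. And a power figure for a four-group omnibus test that includes TD does not show that the study can detect a difference between Groups 1 and 2, the comparison the article relies on to judge the synthesized voices.

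**Working it through.** **1. Is TD in the test?** The analysis section does not say. Three pointers favour inclusion: Groups 2 to 4 are all called controls; all four groups are assessed; and the ASRS questionnaire section gives comparability with a TD control group as a reason for choosing the scale. The power figure is a fourth.

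**2. The plan's own power figure.** One-way ANOVA, noncentral F with λ = f²·k·n. The convention f = d/2, so d = 0.8 gives f = 0.4, reproduces other figures in the article: 6 emotions with 19 words gives 0.916 (stated 0.92); 2 groups of 34 gives 0.902 (stated 0.90). For ASRS:

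| Comparison | k | n | f | Power | Stated |
|---|---|---|---|---|---|
| Groups | 4 | 16 | 0.40 | 0.742 | 0.92 |
| Groups | 4 | 16 | 0.50 | 0.917 | 0.92 |
| Groups | 3 | 16 | 0.50 | 0.860 | 0.92 |
| Sessions | 3 | 18 | 0.50 | 0.902 | 0.90 |

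A single f = 0.5 (d = 1.0) with four groups and three sessions accounts for both ASRS figures. Three groups would need f = 0.55 to reach 0.92. The stated d = 0.8 reproduces neither ASRS figure.

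**3. Baseline, if the qualifying score is reused.** All 18 TD scores lie below all 54 autistic scores. Mean ranks are 9.5 and 45.5; the overall mean rank is 36.5. The smallest possible Kruskal–Wallis statistic is

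H = 12/(72 × 73) × [18 × (9.5 − 36.5)² + 54 × (45.5 − 36.5)²] = 12/5256 × 17,496 = 39.9

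on 3 df (critical value 7.81; p about 1 × 10⁻⁸), whatever happens among Groups 1 to 3.

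**4. Follow-up with no intervention effect.** The documents give no SD, so SD 10 is assumed. With Groups 1 to 3 equal and TD lower by a gap g, f = g × √3/(4 × 10) and λ = 72f². For g = 10, f = 0.433 and λ = 13.5.

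| Gap (T-points) | 5 | 8 | 10 | 12 | 15 |
|---|---|---|---|---|---|
| Omnibus rejection | 29% | 66% | 86% | 96% | 99.8% |

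To see which gaps selection leaves, simulation selected children at 60 and retested them (4,000 runs per scenario; assumed SD 10, TD population mean 50, autistic population mean 55 to 70, screening-to-follow-up correlation 0.5 to 1.0). The smallest gap was about 12 points (60.7 vs 48.5), with 98.4% rejection; all other scenarios gave 99.9% to 100%. In the same runs a three-group ANOVA on Groups 1 to 3 rejected in 4.3% to 5.9%, and Tukey found any difference among the autistic groups in 0.8% to 3.2%.

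**5. Cost to one randomised pair, Tukey branch.** With n = 18 and d = 0.8, the noncentrality is 0.8 × √(18/2) = 2.4. Critical t is the studentized range quantile divided by √2.

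- Three groups, 51 df: 3.414/√2 = 2.41, power 0.50.
- Four groups, 68 df: 3.725/√2 = 2.63, power 0.41.

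**6. Holm–Wilcoxon branch.** When the three TD pairs are all significant, Holm disposes of them first and the autistic pairs face the same thresholds as in a three-pair family. In simulation with TD 1.7 SD below the lowest autistic mean, power with vs without TD was 0.455 vs 0.458, 0.450 vs 0.450 and 0.442 vs 0.442.

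**7. Power for three groups of 18.** At f = 0.4 the omnibus power is 0.726. If d = 0.8 is instead the spread between the extreme groups, f is 0.327 (third group midway) to 0.377 (third group equal to one of the two), and power is 0.54 to 0.67.

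**The case against.** The strongest reply is that the article never says a significant four-group F will be taken as efficacy. It goes on to pairwise tests and within-group time comparisons, and it describes Group 2's role in pairwise terms. That stands. A reader might infer that the whole ASRS group analysis is uninformative or yields false efficacy claims; the documents do not support this, because the pairwise tests among Groups 1 to 3 are valid and not inflated.

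A reader might also infer that significance is guaranteed by construction at every session. It is guaranteed only for the rank test, and only if the qualifying score is reused as baseline. The article does not say it is, and it schedules an ASRS at the 1st session. The follow-up rates rest on assumed values, and regression to the mean can narrow the gap.

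Nor is the loss of sensitivity general: it is confined to the Tukey branch, and entry truncation at 60 makes the rank branch plausible.

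The four-group reading is itself an inference. The ASRS questionnaire section speaks of parents of two groups, and the 0.92 fits four groups only with an effect size other than the stated one.

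Finally, a TD benchmark is a stated purpose and a legitimate one. That argues for keeping the comparison, but not for placing it inside the test of the randomised groups.

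**Conclusion.** The point holds in a limited form. On the four-group reading, which the group list, the control-group wording and the power figure all favour, the ASRS omnibus test mainly reflects eligibility and cannot speak to efficacy. Its rejection rate with an inert intervention is about 86% to 100% for gaps of 10 points or more at SD 10, and selection at 60 left gaps of at least about 12 points in every scenario tried.

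Efficacy information survives in the pairs among Groups 1 to 3, but the ASRS analysis section does not name the decisive ones, and under Tukey each loses about 0.09 of power (0.50 to 0.41 at d = 0.8). The stated 0.92 should not be read as power for those contrasts: it appears to be a four-group omnibus figure at f = 0.5, and the stated d = 0.8 gives 0.74 for that test.

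**What to change.** - Run the ASRS group test and its post hoc family on randomised Groups 1 to 3 only.
- Name Group 1 vs 2 and Group 1 vs 3 as the ASRS efficacy contrasts.
- Report the comparison with TD separately, as a reference outside that family.
- Restate the ASRS group-comparison power for three groups of 18: about 0.73 for the omnibus test at f = 0.4, and about 0.50 for one Tukey pair at d = 0.8. State the number of groups and the effect size used.
- State that the ASRS completed at the 1st session, already scheduled, is the baseline, and not the score that qualified the child.

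The cost is mainly wording; no group, sample size or planned session changes. At most, a parent whose qualifying form would otherwise have doubled as baseline completes it a second time. The downsides are that the TD comparison becomes secondary and the stated power is less favourable.

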##### Statistical analysis on behavioral data

Group comparisons of reaction times will be conducted by a Group × Stimulus (neutral, anger, disgust, fear, happiness, or sadness) repeated measures ANOVAs on each assessment session separately. Time comparisons will be conducted by Assessment Session × Stimulus on each group separately. Normality of reaction times will be assessed by Shapiro–Wilk test. In case of non-parametric distribution of the data, a transformation will be applied. Mauchly’s test of sphericity will be used to evaluate homogeneity of variances and co-variances. In case of violation of sphericity, a Greenhouse-Geisser correction will be applied in order to test main effects significance. Post-hoc comparisons will be conducted to assess specific differences (Tukey procedure).

Group comparisons of number of correct answers will be conducted by one-way ANOVAs for each deviant and assessment session separately. Time comparisons (between assessment sessions) will be tested by one-way ANOVAs on number of correct answers for each deviant and each group separately. Normality and homogeneity of variances will be assessed by Shapiro–Wilk and Bartlett tests, respectively. In case of non-parametric distribution of the data, Kruskal–Wallis test will be applied. *Post hoc* comparisons will be conducted to assess specific differences (Tukey after ANOVA, Wilcoxon tests with *p*-value adjustment by Holm method after Kruskal–Wallis).

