##### Statistical analysis on ERPs data

The statistical significance of ERP components will be tested by comparing their mean amplitudes to zero at ROIs using one-sample *t*-tests. This method will allow us to focus exclusively on significant responses, and to distinguish significant scalp distributions from noise. Statistically significant ERPs will be considered for further amplitude analysis.

Group comparisons will be conducted by Group × ROI repeated measures ANOVAs on each ERP and assessment session separately, for standard stimuli. Similarly, for deviant stimuli, Group × ROI × Deviant repeated measures ANOVAs will be performed.

For standard stimuli, time comparisons will be conducted by Assessment Session × ROI repeated measures ANOVAs on each ERP and group separately. For deviant stimuli, Assessment Session × ROI × Deviant repeated measures ANOVAs will be performed.

Scalp distribution comparisons for standard stimuli will be assessed by Group × Laterality (FP1, F3, F7, T7, C3, P3, P7, O1/AFz, Fz, CPz, Cz, POz, Pz/FP2, F4, F8, T8, C4, P4, P8, O2) repeated measures ANOVAs on each ERP and assessment session separately. For deviant stimuli, Group × Laterality × Deviant repeated measures ANOVAs will be conducted.

For all amplitude analysis, normality will be assessed by Shapiro–Wilk test. In case of non-parametric distribution of the data, a transformation will be applied. Mauchly’s test of sphericity will be used to evaluate homogeneity of variances and co-variances. In case of violation of sphericity, a Greenhouse-Geisser correction will be applied in order to test main effects significance. *Post hoc* comparisons will be conducted to assess specific differences (Tukey procedure).

All statistical analysis will be performed with R software. Level of significance will be set at *p* < 0.05.

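### Stage 3 has no baseline-adjusted or Group × Session comparison of the three randomised groups: improvement is tested only within groups, and efficacy rests on post-only post hoc contrasts that include the non-randomised TD group

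*Protocol article*

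**What the plan says.** The Stage 3 data analysis section sets out two kinds of test for every outcome family.

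- **ASRS, between groups:** "Group comparisons will be conducted by one-way ANOVAs on T-scores for each assessment session and symptom domain". **Over time:** "Time comparisons (between assessment sessions) will be tested by one-way ANOVAs on T-scores for each group and symptom domain".
- **Reaction times:** the group comparison is a Group × Stimulus model, using "repeated measures ANOVAs on each assessment session separately. Time comparisons will be conducted by Assessment Session × Stimulus on each group separately".
- **Correct answers, between groups:** "Group comparisons of number of correct answers will be conducted by one-way ANOVAs for each deviant and assessment session separately". **Over time:** "one-way ANOVAs on number of correct answers for each deviant and each group separately".
- **ERPs, between groups:** "Group × ROI repeated measures ANOVAs on each ERP and assessment session separately", with a parallel Group × ROI × Deviant model for deviants. Time is tested by Assessment Session models in each group separately.

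Post hoc tests follow: Tukey, or Holm-adjusted Wilcoxon after Kruskal–Wallis for ASRS and correct answers.

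Under Participants, Intervention, the autistic children are randomised to Groups 1, 2 or 3, with 18 in each. Group 4 consists of 18 TD children, who are not randomised. All four groups attend every assessment. Of Group 2, which hears human voices only, the protocol says: "This group will help to evaluate the efficacy of the use of synthesized voices in the intervention".

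Eligibility is carried over from Stage 2. Autistic children need ASRS T-scores above 60 on the named domains. For TD children, "children with a score inferior to 60 in all scales will be included".

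**The concern.** Stage 3 asks whether the synthesized voice adds something (Group 1 vs Group 2) and whether the intervention as a whole does (Group 1 vs Group 3). The plan measures every child before the intervention, but uses that measurement only as one more separate group ANOVA and as one level of the within-group time factor. It never compares change between groups and never adjusts for baseline.

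Four things follow.

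- The only tests of improvement are within-group. These cannot show a difference between groups. Read alone, they also mix in practice (the same task is given five times) and, for ASRS, regression to the mean (autistic children are selected on high scores).
- For ASRS and correct answers, the time test is a one-way ANOVA on repeated measurements of the same children, which ignores the pairing.
- The group test is not restricted to the randomised groups. For ASRS it includes a group selected to lie on the other side of the cut-off.
- The contrasts that do bear on efficacy are post-only post hoc comparisons. With 18 per group they give up precision that the collected baseline could supply.

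**Working it through.** **Inputs from the protocol (Participants, Intervention):** 18 per group; four groups, three of them randomised; d = 0.8; correlation among repeated measures 0.5; alpha 0.05. ASRS is collected three times (pre-intervention, then 2 and 6 weeks after the end).

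**Assumed here:** an improvement of 0.5 SD, a TD difference of 0.5 to 1.5 SD, and pre-post correlations of 0.3 and 0.7.

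**1. The plan's own figures.** The protocol gives ASRS power of 0.92 with 16 per group (groups) and 0.90 with 18 per group (sessions). One-way ANOVA power uses noncentrality f²N, with f = d/2 = 0.4. This conversion reproduces other figures in the document: 6 emotions × 19 words gives 0.916 (stated 0.92), and 2 groups × 34 gives 0.902 (stated 0.90). For Stage 3 ASRS it gives 0.742 (4 × 16) and 0.726 (3 × 18), so the stated values are not reproduced. They appear at f = 0.5, that is d = 1.0 (0.917 and 0.902). That mismatch is a separate matter. Here it shows only that groups and sessions were powered as separate one-way tests and that no comparison of change was powered.

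**2. Within-group time tests when two groups improve equally.** Simulation of the ASRS time ANOVA as written (18 children, 3 sessions, correlation 0.5, both follow-ups better by 0.5 SD) gives power p of about 0.20 in each group. The chance that exactly one group is significant is 2p(1−p) = 2 × 0.20 × 0.80 = 0.32. At correlation 0.7 it is 25%. With a 0.8 SD improvement and correlation 0.5 it is about 43%.

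**3. Type I error of the one-way time test.** With no change over time, simulation gives 0.4% at correlation 0.5 and 0.04% at 0.7, against a nominal 5%. Positive within-child correlation inflates the error term, so the test is far too conservative.

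**4. The four-group ASRS omnibus.** Let the three autistic groups be equal and TD children score D SD lower. Group means are then 0, 0, 0, −D, and the noncentrality is 18 × 0.75 × D². At D = 1 this is 13.5, and with 3 and 68 df the test is significant in 86% of trials. At D = 0.5 it is 29%, and at D = 1.5 over 99%.

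**5. Chance baseline imbalance.** The SD of a baseline difference between two groups of 18 is √(2/18) = 0.33 SD.

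**6. Power for Group 1 vs Group 2 at one later session, d = 0.8, 18 per group.** Post-only uses a two-sample t-test with 34 df. Baseline adjustment replaces d by d/√(1−ρ²), with 33 df. The Tukey column uses four groups and 68 df.

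| Analysis | Effective d | Single contrast | Tukey over four groups |
|---|---|---|---|
| Post-only | 0.80 | 0.645 | 0.41 |
| Adjusted, ρ = 0.3 (assumed) | 0.84 | 0.69 | 0.46 |
| Adjusted, ρ = 0.5 | 0.92 | 0.77 | 0.56 |
| Adjusted, ρ = 0.7 (assumed) | 1.12 | 0.90 | 0.76 |

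At ρ = 0.5 the adjustment removes 25% of residual variance, so 18 per group acts like 18/0.75 = 24.

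**The case against.** The strongest reply is that randomisation already makes the later-session contrasts sound. The post hoc tests compare Group 1 with Group 2 and with Group 3 directly after treatment. Under randomisation a post-only comparison is unbiased, so neither an interaction nor a baseline covariate is needed for validity. This stands. A reader might infer that Stage 3 cannot answer its efficacy question at all; the documents do not support that.

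A reader might also infer that efficacy will be declared when Group 1 improves significantly and Group 2 does not. The protocol states no such rule. It states expectations of improvement at the end and follow-up sessions and gives no decision rule. The 32% therefore shows why the time tests must not be read that way. It is not an error rate of the written plan.

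Practice and regression to the mean are expected to act alike in Groups 1–3, and Group 3 is randomised, untreated and fully assessed. Between-group contrasts are therefore protected; only the time tests read alone are exposed.

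Selection around 60 concerns ASRS. It does not by construction affect accuracy, reaction times or ERPs. A significant omnibus does not make Group 1 vs Group 2 significant, because Tukey still controls the pairwise error. Including TD children enlarges the family and leaves the omnibus uninformative about the intervention, but it does not create false efficacy.

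The gain depends on the correlation. The protocol's 0.5 is not restated for correct answers, and at 0.3 the gain is modest.

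The defence that an unseen analysis plan may supply the missing comparison does not succeed. The article names the model, factors, stratification and post hoc test for each outcome, so it has made these choices.

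**Conclusion.** The point holds as a defect of efficiency and interpretation, not of validity. For all four outcome families the plan fixes session-by-session group tests and group-by-group time tests, and leaves out the baseline-adjusted comparison of the randomised groups that the collected data allow.

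The time tests carry no between-group information, and for ASRS and correct answers they are wrongly specified for repeated measurements. The ASRS omnibus is likely to be significant because of the TD group alone if TD children score about 1 SD or more below the autistic children. What remains as evidence on efficacy is a set of unbiased post-only post hoc contrasts, with power of 0.645 at the protocol's d = 0.8 as a single comparison and 0.41 under the planned Tukey. Baseline adjustment at correlation 0.5 would bring these to 0.77 and 0.56.

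These sizes rest on normal outcomes with equal variances, full retention of 18 per group, and the assumed improvement, TD difference and correlations shown above.

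**What to change.** For each outcome, fit one model to randomised Groups 1–3 on the post-baseline values. Use the pre-intervention value as covariate, with Group, Session, Group × Session and a child random effect. Keep Stimulus, ROI or Deviant as additional factors where the plan already uses them.

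Make Group 1 vs Group 2 and Group 1 vs Group 3 the efficacy contrasts, at a session named before data are seen. Which session is the investigators' choice, but for ASRS it must be one of the two follow-ups, because ASRS is not collected at the end session. Report TD children as a reference level outside the efficacy test. State that within-group time tests are descriptive and will not be read as efficacy; if they are kept, use a repeated-measures form.

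The cost is analysis wording and a restated power justification for the new model, since the present one covers group and session comparisons separately. No new data and no additional children are needed to make the change.
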